**Methods/design:**

The rationale and design of a randomized controlled trial examining the effects of a stationary cycling intervention for children with CP are outlined here. Sixty children with spastic diplegic CP between the ages of 7 and 18 years and Gross Motor Function Classification System (GMFCS) levels of I, II, or III will be recruited for this study. Participants will be randomly assigned to either an intervention (cycling) or a control (no cycling) group. The cycling intervention will be divided into strengthening and cardiorespiratory endurance exercise phases. During the strengthening phase, the resistance to lower extremity cycling will be progressively increased using a uniquely designed limb-loaded mechanism. The cardiorespiratory endurance phase will focus on increasing the intensity and duration of cycling. Children will be encouraged to exercise within a target heart rate (HR) range (70 – 80% maximum HR). Thirty sessions will take place over a 10–12 week period. All children will be evaluated before (baseline) and after (follow-up) the intervention period. Primary outcome measures are: knee joint extensor and flexor moments, or torque; the Gross Motor Function Measure (GMFM); the 600 Yard Walk-Run test and the Thirty-Second Walk test (30 sec WT).

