The Institutional Review Boards of the University of Southern California, University of California at Los Angeles, Missouri State University, the State of California, Orthopaedic Hospital in Los Angeles, California and CoxHealth Hospital in Springfield, Missouri granted approvals for this research protocol. This study has a pre-post, control group design with single-blinding. Subjects will be randomly assigned to intervention versus control groups. There are two stratifying variables; age (younger, 7–11 and older, 12–18 years) and selective voluntary motor control ability (good versus fair). Randomization to the intervention or control group will be blocked by these two variables. The assessment of selective motor control ability for children with CP has been described by Staudt and Peacock [33]. Good selective motor control is defined as the ability to isolate knee and ankle movement out of synergy (knee extension with the hip in flexion and ankle dorsiflexion with the knee in extension). Fair selective motor control is defined as the ability to isolate knee movement without obligatory hip movement. Only subjects who demonstrate good selective motor control bilaterally will be placed in the good selective motor control category for stratification. Subjects who have poor selective motor control (cannot isolate knee and ankle joint motion out of synergy) bilaterally will be excluded from the study. All others will be placed in the fair selective motor control category.

Interventions will be performed by physical therapists in community clinics throughout Southern California and Southwest Missouri. Evaluations will take place at the University of Southern California or Missouri State University and will be performed by physical therapists blinded to subject group randomization. Evaluation and intervention physical therapists will attend instructional sessions and receive a written manual of procedures specific to either evaluation or intervention protocols. Performance will be videotaped during mock sessions and scored by members of a standards committee using a checklist of critical components for each protocol. To participate in the study, therapists must achieve a minimum score of 90% accuracy. In addition, they will be provided with feedback for aspects of the protocol that are not performed optimally.

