### Cycling intervention protocol

Thirty exercise sessions will occur over a 12-week period. The optimal frequency is three times per week over a ten-week period; however, this alternative schedule provides flexibility for vacations, illnesses or other events. Each session will last approximately 60 minutes. Subjects will be asked to wear shorts and tennis shoes during each session for comfort, safety and assessment purposes. They will receive individualized instruction for an independent self-stretching exercise program for bilateral hip flexor, knee extensor, knee flexor, and ankle plantar flexor muscles as a 5–10 minute warm-up prior to cycling. Additional muscle groups that exhibit reduced range of motion may be included in the stretching program for individual subjects. The cycling intervention will be divided into two phases: 1) Lower extremity strengthening and 2) Cardiorespiratory endurance.

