### Outcome measures

#### Outcome data collection sessions

For the Los Angeles site, data collection will take place at the Division of Biokinesiology and Physical Therapy at the University of Southern California and the Francisco Bravo Medical Magnet High School Gymnasium, Los Angeles Unified School District. Missouri site data collection will take place at Missouri State University. An interpreter will be present for parents or guardians who are non-English speaking. Measurements of subject height and weight will be obtained during each session. For the control group, follow-up evaluations will be scheduled within 10–12 weeks after the baseline evaluation. For the intervention group baseline data will be collected within a one-month period prior to the initiation of intervention sessions. Follow-up data will be collected within a two-week period following the last intervention session.

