### Data analyses

Student t-tests (if normally distributed) or Wilcoxon rank sum tests (if non-normal) will be used to contrast the change from baseline within and between the intervention and control groups for the primary hypotheses. Analysis of covariance procedures will be used to contrast changes adjusting for selective voluntary motor control (good versus fair) and age group (younger, 7–11 years) and (older, 12 – 18 years) for primary outcome measures.

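### Follow-up is timed from baseline in controls (10–12 weeks) but from the last session in the cycling arm (about 10–18 weeks after baseline), so elapsed time is partly tied to arm and a late visit could unblind an evaluator who knows the baseline date

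*Protocol article*

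**What the plan says.** The article's section on outcome data collection sessions gives each arm its own clock.

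- Control arm, counted from baseline: "For the control group, follow-up evaluations will be scheduled within 10–12 weeks after the baseline evaluation".
- Cycling arm, before training: "For the intervention group baseline data will be collected within a one-month period prior to the initiation of intervention sessions".
- Cycling arm, after training: "Follow-up data will be collected within a two-week period following the last intervention session".

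The length of training comes from two places. The abstract says "Thirty sessions will take place over a 10–12 week period". The cycling intervention protocol says "Thirty exercise sessions will occur over a 12-week period" and adds "The optimal frequency is three times per week over a ten-week period", with the longer period allowed for illness, vacations and similar events.

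Under Methods/design, evaluations "will be performed by physical therapists blinded to subject group randomization". Under Data analyses, t-tests or rank sum tests "will be used to contrast the change from baseline within and between the intervention and control groups for the primary hypotheses". The covariates named for the adjusted analysis are selective motor control and age group; time since baseline is not among them. The section on physical activity calendars has every child start the calendar after baseline and hand it back at the follow-up evaluation. Nothing in the article matches the baseline-to-follow-up interval between the arms.

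**The concern.** The primary comparison is of change from baseline in children aged 7 to 18. If one arm is measured later than the other, whatever changes with time alone (growth, maturation, season) enters the difference between arms together with the cycling effect. This needs no missed sessions; it follows from the windows themselves.

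The second issue is the evaluator blind. It is the only blind in the design, since families are told the assignment after baseline. Several primary outcomes are open to examiner expectation: GMFM items are scored 0 to 3 by the evaluating therapist, and the torque and 600-yard tests are run with verbal encouragement. If timing gives the arm away for some children, that protection is weakened for them.

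**Working it through.** **Inputs.** Control interval: 10–12 weeks. Cycling lead-in: 0 to one month. Programme: 10–12 weeks. Lag after the last session: 0–2 weeks. All are from the article. A month is taken as 4 to 4.43 weeks (31 days).

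**The plan's own figure.** 30 sessions / 3 per week = 10 weeks, which agrees with the stated optimal schedule.

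**Range of the cycling interval** = lead-in + programme + lag.

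- Minimum: 0 + 10 + 0 = 10 weeks. Counting from first to last session on a Monday/Wednesday/Friday pattern gives (9 × 7 + 4)/7 = 9.6 weeks.
- Maximum: 4 + 12 + 2 = 18 weeks, or 4.43 + 12 + 2 = 18.4 with a 31-day month.
- Beyond the control limit: 18 − 12 = 6 weeks (6.4 with a 31-day month).
- Weeks 10–12 are common to both arms.

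**Mean interval if each window is used uniformly (assumption).** Cycling: 2 + 11 + 1 = 14 weeks. Control: 11 weeks. Difference: 3 weeks. With a month of 4.34 weeks the cycling mean is 14.17 and the difference 3.17.

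**Share of cycling visits after week 12.** This happens when lead-in + (programme − 10) + lag exceeds 2 weeks. With full uniform windows the share is 1 − (2³/6)/(4 × 2 × 2) = 0.917, or 0.923 with a month of 4.34 weeks. Other uses of the windows:

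| Use of the windows | Mean interval (weeks) | Share after week 12 |
|---|---|---|
| Programme always 12 weeks, gaps uniform over the full windows | 15.0–15.2 | 100% |
| All three windows uniform | 14.0–14.2 | 92% |
| Programme always 10 weeks, gaps uniform over the full windows | 13.0–13.2 | 75–77% |
| Lead-in up to 2 weeks, lag up to 1, programme uniform | 12.5 | 71% |
| Lead-in up to 1 week, lag up to 1, programme uniform | 12.0 | 50% |
| Lead-in up to 1 week, lag up to 0.5, programme uniform | 11.75 | 38% |
| Programme 10 weeks, gaps of at most 1 week each side | at most 10 + 1 + 1 = 12 | 0% |

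**Size of a growth effect.** The article gives no growth rate. Assume that knee torque grows 10–15% a year.

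- Extra 1.5 weeks (12.5 − 11) at 10%: 1.5/52 × 10% = 0.3% of the mean.
- Extra 3.2 weeks (14.2 − 11) at 15%: 3.2/52 × 15% = 0.9%.
- A single child at the far end (18.3 − 11 = 7.3 weeks) at 15%: 2.1%.

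No comparable figure can be formed from the article for the GMFM or the walking tests.

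**The case against.** The strongest reply is that the visit date does not, by itself, reveal the arm. An evaluator would need both the child's baseline date and the arm-specific rule. The article does not say that evaluators have either, that they book visits, or that one therapist does both evaluations. Evaluations are at the universities, treatment is in community clinics, and the therapists' manuals are specific to one role or the other. Who sees what is an operational detail that an article may leave to the full protocol. This stands, so the blinding risk is conditional. One route is nonetheless visible in the text: a calendar begun after baseline, returned at the follow-up session and running past 12 weeks would point to the cycling arm.

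A reader might also infer that every cycling child has at least as much time as every control. That is wrong: a cycling child tested promptly after ten weeks precedes a control tested at week 12.

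The one-month and two-week limits are tolerances, not schedules. The 92% rests on assumed uniform use, and anything from 0% to 100% fits the text. This also stands.

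Nor can it be said that adjustment is impossible or that the net effect must favour cycling. The windows overlap and the interval varies within each arm, so elapsed time can be modelled, though adjustment for later visits would rest largely on extrapolation. A lag after the last session could also let training gains fade. Finally, torque is read from a dynamometer and GMFM sessions are filmed, which limits examiner influence. But the film is for review when a score is questioned, and neither measure equalizes the timing.

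**Conclusion.** The point holds as a defect of scheduling. The stated rules give about 10–18 weeks for cycling children who complete all 30 sessions, against 10–12 weeks for controls. A longer mean interval in the cycling arm is probable, about three weeks under uniform use of the windows, but it is not certain for any one child. Elapsed time is therefore partly confounded with arm. On the assumed growth rates the consequence for torque is small, below 1% of the mean on average.

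The risk to blinding matters more but is conditional: an on-schedule visit after week 12 identifies a cycling child only to someone who knows the baseline date and the rule, and a visit in weeks 10–12 fits either arm. The document does not support the stronger reading that the blind is broken, or that growth could account for a material treatment difference.

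**What to change.** Apply one timing rule to both arms. At randomization, give each control child a notional start date, with the same lead-in of up to one month, the same 10–12 week period and the same two-week follow-up window. Yoking each control's visit to that of a cycling child would serve equally and would also match how the windows are used in practice. A single fixed window from baseline is less suitable, because it could fall before a slow attender's last session.

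Keep baseline dates off the evaluators' follow-up forms, and have the activity calendars handed to someone other than the evaluator.

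The cost is modest: no extra visits or staff. Controls would wait about three weeks longer on average under uniform use (14 against 11 weeks), and some up to about 18 weeks. Their calendars, now set for a 12-week period, must be extended, and the bicycle or tricycle given on completion would reach them later.

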#### Outcome data measurements

Outcome measures for this study include assessments at the body function and structure, activity and participation levels of the ICF. Primary outcome measures are: 1) knee joint extensor and flexor torque; 2) the Gross Motor Function Measure (GMFM) Sections D: Standing and E: Walking, Running and Jumping [38]; 3) the 600 Yard Walk-Run test [39] and 4) the Thirty-Second Walk test (30 sec WT) [40]. Secondary measures are: 1) the Pediatric Outcomes Data Collection Instrument (PODCI) [41], 2) the Pediatric Quality of Life Inventory™ (PedsQL) [42-44] and 3) instrumented gait analysis.

Knee joint extensor and flexor moments, commonly referred to as joint torque in a clinical setting, are measures at the body function and structure level of the ICF. A Kin-Com dynamometer (Chattanooga Group Inc., Hixson, TN) will be used for data collection at the Los Angeles site and a Biodex Multijoint System (Biodex Medical Systems Inc., Shirley, NY) at the Missouri site. The subject will be seated with the trunk slightly reclined. Straps at the waist, chest, thigh and distal aspect of lower leg will be used to secure the subject to the testing device. The axis of the device's moving arm will be aligned with the subject's knee joint center. The subject will be directed to observe the computer screen for visual feedback while being verbally encouraged by the investigator to provide maximum effort. Five repetitions of knee joint extension and flexion at 0, 30, 60 and 120 degrees/second will be performed bilaterally. The peak joint moment for each group of five contractions will be determined.

The GMFM assesses performance at the activity level of the ICF. It has been shown to be valid [45] and reliable [46] for assessing children with CP. Two of the five dimensions, Dimension D: Standing (13 items) and Dimension E: Walking, running, and jumping (24 items) will be tested. GMFM sessions will be videotaped to permit review should a question about a particular score arise. Subjects will wear shorts and be tested barefoot and without assistive devices or ankle-foot orthoses. The evaluation therapists will follow the procedures outlined in the Gross Motor Function Measure User's Manual [38] for testing and scoring. Each item will be scored as 0 = does not initiate, 1 = initiates, 2 = partially completes, 3 = completes or NT = not tested. The data will be analyzed using the GMFM-66 Ability Estimator Software. The advantage of the software is the conversion of the ordinal data into an interval scale. This will allow for a more accurate estimate of the child's ability and provide a measure that is equally responsive to change across the spectrum of ability levels [38].

The 600 yard walk-run test [39] assesses walking and/or running endurance at the activity level of the ICF. This test is an indirect measure of cardiorespiratory fitness and is reflective of a child's ability to participate in play and sport activities. It is a standardized physical fitness test developed for school-age children. Fernhall et al. [39] used this test for children with intellectual disabilities and found a high correlation with laboratory measures of peak V0_2_. During this test, children are asked to complete a 600 yard distance as fast as possible by running, walking or a combination of both. The distance required will be clearly explained so they may pace themselves. Orange cones will be placed to visibly mark the perimeter of the circular path. Subjects will be encouraged verbally to continue walking or running until they complete the 600 yard distance. If a subject cannot complete this distance within 15 minutes or stops for more than five seconds, the test will be stopped. At the end of the test, the distance completed and the time will be recorded. Distances of less than 600 yards will be measured using a distance-measuring wheel. Outcomes include the distance the child is able to complete, the time for completion and the speed.

The 30 sec WT assesses walking function at the activity level of the ICF and is reflective of a child's ability to walk within the school environment. Normative data for 227 children between the ages of six and 13 years are available for comparison [40]. This test will be administered in a gymnasium by asking the subject to walk at a comfortable speed and to stop when 30 seconds have elapsed. Children will be instructed to walk as if they were the leader in a line at school. The examiner will monitor time using a stopwatch. When 30 seconds have elapsed, the examiner will instruct the subject to "freeze" and not move until his or her foot position is marked. The distance from the starting line to the heel of the forward-most foot will be measured using a distance-measuring wheel. Outcomes will be the total distance walked and walking speed.

The health-related quality of life questionnaires to be used for this study assess multiple domains of function within the ICF but focus on environmental and personal contextual factors. Questionnaires will be administered in an interview format. The PODCI Scale was developed to assess health-related quality of life in children from 7 – 19 years of age. It demonstrated good reliability, construct validity and sensitivity to change over a 9-month period [41]. This questionnaire will be completed by the parent, or guardian, and all adolescents (11–18 years). Individuals will be asked to respond to questions by choosing from a list of possible answers. A Spanish language version of this tool will be available. Interpreters will be made available for other languages. There are eight scales: upper extremity and physical function, transfer and basic mobility, sports/physical functioning, pain/comfort, treatment expectations, happiness, satisfaction with symptoms and a global functioning scale (a combined scale calculated from the first four scales). All components are transformed to a 0–100 scale for analyses.

The PedsQL is a health related quality of life instrument specifically designed for children with disability [42-44]. It has been found to be a reliable and valid tool for children aged two to 18 years and was found to be sensitive to age, acute versus chronic disability and unaffected children versus those with disability [42]. This questionnaire will be administered to all subjects in the study. Children will be interviewed using a self-report questionnaire separately from their parents to avoid parental influence. Three different age versions will be used: Young children (5–7 years), Children (8–12 years) and Teen (13–18 years). The children will be asked "In the past one month, how much of a problem has this been for you ...?". A three point Likert scale is used for the Young Child category with responses ranging from 0 (Never) to 4 (Almost Always) and a five point scale is used for the other two age categories. Four separate dimensions are assessed: Physical functioning, Emotional functioning, Social functioning and School functioning. The latter three dimensions are combined to create a Psychosocial Health Summary Score. Items are reverse scored and linearly transformed to a 0–100 scale for analyses.

Gait data will be collected in the Musculoskeletal Biomechanics Research Laboratory at the University of Southern California for a subset of children. Subjects will wear shorts and be barefoot during walking trials at self-selected and maximum walking speed. Hand-held assistance will be allowed, as needed, for safety. Three-dimensional kinematics will be acquired using an 8-camera VICON motion analysis system (Oxford, UK) with a sampling frequency of 60 Hz. Ground reaction forces will be acquired with 3 AMTI force platforms (Watertown, MA) imbedded in the walkway. Joint angles and net joint moments (inverse dynamics approach) will be computed using Visual 3D software (Gaithersburg, MD). Hip, knee and ankle kinematics and temporal data will be calculated for all trials. Joint kinetics will be calculated for trials where the subject's foot makes isolated contact with the force plate.

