If the subject qualifies during the in-person screening, enrollment procedures will occur. An investigator will explain the informed consent, medical release, photo consent and a summary of the Health Insurance Portability and Accountability Act of 1996 (HIPAA) policy to the participants and their guardians. Testing purposes and procedures, the randomization process, potential risks and benefits for participants and responsibilities of both the participants and the research team will be discussed and questions answered. If the individual and their parent/guardian decide to proceed with enrollment, the consent form will be signed and an enrollment form, containing the subject's age and selective motor control ability, will be submitted to the PTClinResNet Data Management Center for subject randomization. Families will be notified of their child's assignment to the control or intervention group following the baseline evaluation.

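### Knee torque is measured on a different dynamometer at each site, but site is in neither the strata nor the stated models, leaving chance imbalance, some loss of precision and possibly mixed torque scales

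*Protocol article*

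**What the plan says.** All places are in the Protocol article.

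- **Outcome data measurements** lists torque first: "Primary outcome measures are: 1) knee joint extensor and flexor torque". On equipment it says "A Kin-Com dynamometer (Chattanooga Group Inc., Hixson, TN) will be used for data collection at the Los Angeles site and a Biodex Multijoint System" at the Missouri site. The section describes one positioning and repetition procedure for both machines, and no cross-calibration.
- **Methods/design**: "There are two stratifying variables; age (younger, 7–11 and older, 12–18 years) and selective voluntary motor control ability (good versus fair"). It continues: "Randomization to the intervention or control group will be blocked by these two variables".
- **Subjects**: after consent, "an enrollment form, containing the subject's age and selective motor control ability, will be submitted to the PTClinResNet Data Management Center for subject randomization". Site is not among the contents described.
- **Data analyses**: t-tests or Wilcoxon tests "will be used to contrast the change from baseline within and between the intervention and control groups for the primary hypotheses". The ANCOVA is to "contrast changes adjusting for selective voluntary motor control (good versus fair) and age group". Neither site nor device is named.
- **Sample size** bases the power analysis on joint moment data, that is, on the outcome measured with two machines.

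**The concern.** Every torque value from Missouri comes from a different machine than every torque value from Los Angeles. Evaluation venues and treating clinics also differ by region. The article nevertheless names its strata and covariates explicitly, and site is in neither list.

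Three things are at stake:

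1. Allocation does not control site, so the arms may by chance hold different shares of Missouri children. If change differs by site, that shifts the estimate in the trial as run.
2. Without a site term, any difference in change between sites goes into the residual variance and costs power.
3. Change from baseline removes a constant offset between machines but not a scale factor. If one machine reads proportionally higher, the pooled raw change mixes two units.

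**Working it through.** **Inputs from the article.** 60 children, 30 per group; effect size 0.7; two-sided 0.05; two-group t-test; stated power 80%.

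**Assumptions, because the article gives no figure.** Missouri children M = 10 to 30 of 60; site difference in change 0 to 1.0 SD; device scale factor 1.10 to 1.20. Allocation is treated as 30 v 30 without regard to site, and attrition is ignored in steps 1 to 4.

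**1. Reference power.** The noncentral t gives 76.0% for 30 per group at 0.7 (normal approximation 77.4%), not 80%. That shortfall is a separate matter; 76.0% serves here only as the baseline for comparison.

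**2. Chance imbalance by site.** The number of Missouri children in the cycling arm is hypergeometric. For M = 20:

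- variance = 20 × 0.5 × 0.5 × (40/59) = 3.39, so SD = 1.84 around a mean of 10;
- 7 to 13 covers 94.6% of allocations, and 6 to 14 covers 98.7%;
- SD of the between-arm difference in Missouri share = 2 × 1.84/30 = 12 percentage points;
- a 13:7 split or worse is a difference of at least 13/30 − 7/30 = 20 points, with probability 17%.

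For other splits the chance of 20 points or more is 8% (M = 10), 7% (M = 15) and 20% (M = 30). The expected difference is 0 in every case.

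Shift in the estimate = imbalance × site difference in change. With 20 points and an assumed 0.5 SD this is 0.20 × 0.5 = 0.10 SD, and 0.10/0.7 = 14% of the design effect.

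**3. Precision without a site term.** With Missouri share p and site difference D (in SD of change), the pooled variance is 1 + D²p(1 − p), so the effective standardized effect is 0.7/√(1 + D²p(1 − p)).

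| D | p | variance | effective d | power, 30 per group |
|---|---|---|---|---|
| 0.25 | 0.25 | 1.012 | 0.696 | 75.5% |
| 0.25 | 0.50 | 1.016 | 0.695 | 75.4% |
| 0.5 | 0.25 | 1.047 | 0.684 | 74.1% |
| 0.5 | 0.50 | 1.063 | 0.679 | 73.5% |
| 1.0 | 0.25 | 1.188 | 0.642 | 68.7% |
| 1.0 | 0.50 | 1.250 | 0.626 | 66.4% |

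Simulation (8,000 randomizations per setting, M = 15 and 30) agrees: without a site term, power is about 76% at 0 to 0.25 SD, 74% at 0.5 SD and 67 to 68% at 1.0 SD. With a site term it stays at 75 to 76%. Type I error is about 4 to 5% and mean bias about 0 in both analyses.

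**4. Scale difference between devices.** Take M = 20, a true effect of 0.7 SD on the Los Angeles scale and no mean change in controls. With scale factor k and a Missouri children in the cycling arm, the pooled difference is 0.7 × [1 + (k − 1) × a/30].

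| k | a = 10 | a = 14 | a = 6 | shift from balance |
|---|---|---|---|---|
| 1.10 | 0.723 | 0.733 | 0.714 | 0.009 SD |
| 1.20 | 0.747 | 0.765 | 0.728 | 0.019 SD |

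At k = 1.10 the variance is (1/3) × 1.21 + 2/3 = 1.07, so the standardized effect is 0.723/√1.07 = 0.699 and power is 75.9%. At k = 1.20 the variance is 1.147, the standardized effect 0.697 and power 75.7%. A scale factor of this order mainly blurs the unit of the pooled estimate; it hardly affects power.

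**5. Which remedy meets which problem.** An additive site term absorbs a difference in mean change. It does not correct a scale factor: if Missouri torque is k times Los Angeles torque, the Missouri change is still k times too large relative to Los Angeles. On the log scale, log(k × post) − log(k × pre) = log(post) − log(pre), so k cancels.

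**The case against.** A reader might infer that device is confounded with group, or that the torque comparison is biased. The documents do not support that. Children are randomized individually, no site or machine is tied to an arm, and each child's change is taken from that child's own baseline. Site is therefore independent of group in expectation, and the simulations show mean bias near 0 and type I error kept.

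A reader might also infer a large power loss. That needs a site difference in change of about 1.0 SD, which nothing in the article suggests. The plan has safeguards too: common training, a written manual, a 90% accuracy threshold for therapists, blinded evaluators, and one positioning and repetition procedure for both machines. Finally, this is a condensed article, and calibration details or further covariates may be set out in a manual or analysis plan that is not shown.

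Most of this stands and limits the point to precision and chance imbalance. It does not remove the point. Therapist training does not make two machines read alike, and the article states its strata and covariates as specific lists without site. A later plan could add a site term but could not change allocations already made on two factors. The cancellation of a device offset also needs both tests at the same site, which is implied but not stated.

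**Conclusion.** The point holds as one of precision and robustness. Site, and with it device, is missing from the stated strata and the stated models, although torque is a primary outcome and the power basis.

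The consequences are modest under plausible assumptions. Power falls by about 2 points if change differs by 0.5 SD between sites, and by 8 to 9 points only at 1.0 SD. With 20 Missouri children there is a 17% chance of a 20-point imbalance between arms, which at 0.5 SD moves the estimate by 0.10 SD. Imbalance combined with a 10% device scale factor moves it by only about 0.01 SD, even at a 14:6 split. All of these rest on an assumed site split and assumed site or device differences. The change is worth making because it costs almost nothing, not because the trial would otherwise be invalid.

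**What to change.** 1. In Data analyses, add site as a fixed covariate, together with the baseline value, to the ANCOVA for each primary outcome. The site term belongs with all of them because venues and clinics differ by site, not only the dynamometers. Cost: one degree of freedom for site; in the simulations with no site difference, power changed by at most 1 point.
2. Analyse torque on a log scale (percent change), or standardized within device, at least as a sensitivity analysis, because the site term does not correct a scale factor. Cost: a little more analysis. The log effect is read as a ratio and needs positive torque values. Within-device standardization avoids that limit but depends on an SD estimated from each site's smaller sample.
3. State that each child is tested at the same site, on the same device, at baseline and follow-up, and report whether the two machines were cross-calibrated.
4. Optional: record site on the enrolment form and stratify further enrolment by it. This makes 2 × 2 × 2 = 8 cells, on average 60/8 = 7.5 children each, so incomplete blocks could weaken balance on age and motor control. The covariate in item 1 recovers most of the precision without this trade-off.
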